#### Data collection

The data collection will be organized and supervised by the coordinating center. All quantitative data will be collected electronically into a common database, located at the REDCap system of the University Medical Centre Hamburg-Eppendorf (REDCap, www.project-redcap.org). This will minimize data exchange between countries. Qualitative data will be generated on a national level and securely stored at each site. The focus group discussions will be audio-recorded and transcribed verbatim. The audio records will be deleted after the transcripts have been generated.

### Data handling

Individual participant data will be collected and processed in a de-identified form by a unique study identification number (ID). All data directly identifying persons will be replaced by the study ID. No data allowing participant identification will be handed to third parties. Data collected locally from the individual partners (original consent forms, audio files, and interview transcripts) will be securely archived at the specific sites for maximum 10 years after publication of the last scientific report, following the national data management strategy. If locally collected data is exchanged between partners, then only in fully anonymized form. For locally collected data, compliance with the GDPR will be determined in the data protection agreement. In accordance with the data minimization principle, we will only collect data that is relevant to the purposes of the project.

### Data analysis

We will calculate descriptive measures of all variables and examine group differences at baseline. Our primary hypothesis within the RCT will be tested with a hierarchical linear model including time (two-staged) and group as factors, time as repeated effect, the time x group interaction, the baseline outcome score as a covariate, and a random intercept. We will use the restricted maximum likelihood method to produce estimates. To assess group differences for each time point, we will determine estimated marginal mean values (EMMeans). Effect sizes will be calculated by dividing the adjusted group mean difference by the observed standard deviation of the total sample at baseline. Model assumptions will be checked by plotting residuals against estimated values and residual distribution against normal distribution. We will perform all tests two-sided and consider *p* < 0.05 as statistically significant. Data will be imputed if more than 5% are missing. In accordance with White et al. [51], the number of imputations will be chosen depending on the proportion of missing data.

Quantitative data will be analyzed descriptively (mean, standard deviation, percentages, figures). Qualitative data will be analyzed with qualitative content analysis according to Mayring [52]. We will deductively derive implementation barriers and facilitators based on the CFIR (www.cfirguide.org), i.e. considering the outer and inner setting, intervention characteristics, individuals involved, and the process. Based on these contextual conditions, we will derive implementation strategies with the CFIR.

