### Study setting

The study will be conducted in routine care of patients with rare autoimmune liver diseases at five different centers: The University Medical Center Hamburg-Eppendorf (UKE) in Germany, the University Health Network in Toronto, Canada, the Ghent University Hospital in Belgium, the Medical University of Warsaw in Poland, and the University of Debrecen in Hungary. The UKE serves as coordinating center and is in charge of the study conduct. Patients will be recruited in routine care but participate from home and data will be collected centrally online by the coordinating center in Germany.

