#### Sample size

Our primary effectiveness outcome is the group difference in the baseline-adjusted mean score in mental health-related quality of life at post-assessment, assessed with the Short-Form Health Survey (SF-12 [28]). Taking the results of our prior randomized controlled trial (RCT) into account [15], we assume a between groups effect size of *d* = 0.4. Based on two-sided testing with α = 0.05 and 1-β = 0.8, *N* = 100 patients are needed per group (intention-to-treat analysis), yielding in *N* = 200 to be analyzed. Considering our prior RCT [15], we conservatively expect an inclusion rate of 60% and approximately 15% loss to follow-up. Thus, *N* = 240 patients will be included, for which we expect to invite a total of *N* = 400 patients for participation at the five study sites over 15 months.

For the quantitative implementation part of the trial, all patients in the intervention group (*N* = 100), all peer-counselors (~ *N* = 40) and all involved healthcare providers (~ *N* = 25) will be invited to participate in the survey. With an estimated response rate of 80% [15], we expect to include *N* = 132 participants across all sites. At least *N* = 5 participants per stakeholder group and site will be invited to take part in the focus groups, resulting in an estimated sample size of *N* = 100 in total.

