#### Methods against bias

A fixed randomization schedule (allocation ratio 1:1) will be conducted electronically to avoid any preferential patient allocation to the two conditions. Randomization will be conducted by a researcher who is not involved in data assessment and intervention delivery. Neither the patients nor the researchers have any influence on the randomization procedure. *Electronic data collection.* Data will be directly entered into electronic databases by the patients. Thus, error-prone transfer from paper to the electronic databases will be avoided. *Standardization of intervention.* Peer-counselors will be trained and supervised and the intervention is described in peer-counseling guidelines. After each session, peer-counselors will complete a short protocol to assess adherence to the program content. *Blinding.* a) Raters: Outcome assessments will be either self-reported or performed by trained raters who are fully blinded regarding group allocation and not involved in intervention delivery. Thus, Q.RARE.LI is fully observer-blinded. b) Peer-counselors and patients: As in most psychotherapeutic intervention studies, full patient and therapist blinding is not feasible as their active involvement in the intervention is necessary. However, peer-counselors will not be informed about the patient’s group allocation. *Minimization of patient drop-out.* At follow-up, patients will be contacted by telephone according to a schedule of repeated contact attempts. *Standardized report of trial and results.* The trial and the results will be reported according to the CONSORT 2010 recommendations (www.consort-statement.org/).

All data on human subjects will be recorded, handled, and stored by the rules of the General Data Protection Regulation (GDPR). A Data Safety and Monitoring Board (DSMB), independent of the project team and consisting of internationally recognized experts in rare diseases and psychosocial treatments, will oversee the conduct of this study. Before the trial starts, we will prepare a data management plan and all partners will sign a data protection agreement in which they commit to comply to the GDPR.

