## Discussion

Q.RARE.LI aims to pave the way for widely available psychosocial support for the rare disease community. We expect to demonstrate the effectiveness of the peer-delivered psychosocial support intervention in routine care of patients with rare autoimmune liver diseases in five different national health systems. With respect to implementation outcomes, we expect high acceptability and perceived feasibility of the intervention from the perspective of patients, peer-counselors, and healthcare providers. In addition, we expect to gain a deep understanding of the implementation context in five different countries and be able to derive barriers and facilitators for implementation based on the CFIR framework. This will lead to a profound understanding of the intervention characteristics, the outer setting, the inner setting, the individuals involved as well as the process from different perspectives (including patients and healthcare providers). Identifying these contextual determinants will help us to derive appropriate implementation strategies and develop a concrete implementation plan in each country. If our hypotheses are confirmed, we will be one step closer to making targeted psychosocial support available to a large group of patients with rare diseases. Independent of the effectiveness results, the results on implementation will lead to a better understanding of the implementation conditions in five different healthcare settings and facilitate future implementation of any psychosocial support program.

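### The primary model as listed has no site or country term in a trial pooling five countries; adding one is nearly free and gains modest precision

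*Protocol article*

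**What the plan says.** The Data analysis section of the protocol article gives the primary model term by term. It opens with "Our primary hypothesis within the RCT will be tested with a hierarchical linear model including time (two-staged) and group as factors" and adds time as a repeated effect, the interaction of time with group, adjustment for the baseline score, and one random intercept. It also fixes the estimation method (restricted maximum likelihood) and the effect-size denominator. It names neither site nor country, and it does not say to which level the random intercept belongs.

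On setting, Study setting states: "The study will be conducted in routine care of patients with rare autoimmune liver diseases at five different centers", one each in Germany, Canada, Belgium, Poland and Hungary. The section on peer-counselors has each partner recruit about seven to ten of them and train them at the national site. Informed consent provides for written information in the local language. The Discussion expects to show effectiveness "in routine care of patients with rare autoimmune liver diseases in five different national health systems".

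On allocation, Methods against bias says only: "A fixed randomization schedule (allocation ratio 1:1) will be conducted electronically to avoid any preferential patient allocation to the two conditions". Strata and blocks are neither described nor excluded.

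The target is defined under Sample size: "Our primary effectiveness outcome is the group difference in the baseline-adjusted mean score in mental health-related quality of life at post-assessment".

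**The concern.** Site is bound up with much that could move the outcome: the health system that defines care as usual, the counselors and their training, and probably the language in which the questionnaires are answered (an inference, since the article mentions local language only for written information). It is the most obvious prognostic grouping in the design. The model is written out rather than deferred, so this is a stated model without a major design factor, not detail left to a fuller document.

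At stake is efficiency, and agreement between design and analysis. Between-site variance that is not modelled stays in the error term. If allocation was balanced within sites, the analysis does not take credit for that balance.

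**Working it through.** **1. The plan's own figures.** Under Sample size the standardised difference is 0.4 by assumption, and the calculation is described as follows: "Based on two-sided testing with α = 0.05 and 1-β = 0.8, *N* = 100 patients are needed per group".
- Normal approximation: n = 2 × (1.960 + 0.842)² / 0.4² = 98.1, so 99 per group. With the noncentral t distribution it is 100 per group, power 0.804.
- Attrition, for which the same section says "we conservatively expect an inclusion rate of 60% and approximately 15% loss to follow-up": 200 / 0.85 = 235.3, so 236, against 240 planned; 240 × 0.85 = 204 analysed; 400 × 0.60 = 240.

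The stated figures reproduce.

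**2. Power with and without a site term.** Let r be the share of baseline-adjusted outcome variance between sites. The document gives no value, so r is an assumption. Power at 100 per group is Φ(δ × √50 − 1.96), where δ is the effect divided by the SD that remains in the model. A site term reduces that SD by the factor √(1 − r). The article does not say whether d = 0.4 refers to the total or the within-site SD. Both are shown.

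| r (assumed) | d on total SD: without site | with site | d on within-site SD: without site | with site |
|---|---|---|---|---|
| 0.01 | 0.807 | 0.811 | 0.804 | 0.807 |
| 0.05 | 0.807 | 0.827 | 0.787 | 0.807 |
| 0.10 | 0.807 | 0.846 | 0.765 | 0.807 |

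Example for r = 0.10, total SD: δ = 0.4 / √0.90 = 0.4216; 0.4216 × √50 = 2.981; Φ(2.981 − 1.96) = 0.846.

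**3. Simulation.** 200 patients, five equal sites of 40, one post-baseline time point, 10,000 runs per cell, d = 0.4 on the total SD for power.

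| r | Allocation stratified by site | Type I error: without site | with site | Power: without site | with site |
|---|---|---|---|---|---|
| 0.05 | no | 0.0487 | 0.0505 | 0.8030 | 0.8145 |
| 0.05 | yes | 0.0434 | 0.0508 | 0.8135 | 0.8179 |
| 0.10 | no | 0.0506 | 0.0506 | 0.8128 | 0.8438 |
| 0.10 | yes | 0.0442 | 0.0525 | 0.8250 | 0.8349 |

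Monte Carlo standard errors are about √(0.05 × 0.95 / 10,000) = 0.002 for type I error and √(0.81 × 0.19 / 10,000) = 0.004 for power. So 0.043 and 0.044 are not distinguishable from each other, but both lie below 0.05. Without stratification the unadjusted test holds its level. With stratification it is mildly conservative, and the power differences are close to simulation noise.

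**4. How far chance site imbalance can move the contrast.** With 204 analysed and unstratified allocation, the part of the treatment difference due to site has SD √(4/204 × r × 4/5): 0.013 at r = 0.01 and 0.040 at r = 0.10, in outcome SDs. The standard error of the contrast is √(4/204) = 0.14. This is the same cost as the loss of precision in step 2, not a second one.

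**5. What a site term does not do.** If the treatment effect itself varied across sites with an assumed SD of 0.2, simulated type I error for the average effect over a wider population of sites was about 0.09 without a site main effect and about 0.10 with one. A main effect for site does not address that question.

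**The case against.** The strongest reply is that the gain is small and hypothetical. No between-site variance is given anywhere, and the baseline score already in the model will absorb much of any stable difference in level between countries or language versions. The residual site share may therefore be near the low end, where power moves only from 0.807 to 0.811. This stands, and it limits the size of the point. It does not remove it, because the term costs only 4 degrees of freedom.

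A second reply is that the model is called hierarchical and its random intercept might be for site. The wording does not exclude this. Beside a repeated time effect, however, the patient is the natural reading, and an analyst should not have to guess.

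A reader might also infer that randomisation is not stratified by site. The article does not support that: it is silent on strata and blocks, which a condensed article commonly leaves to the full protocol. Any probability of lopsided sites worked out for simple allocation rests on that silence.

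Nor do the documents promise a confirmatory result for each country. The hypothesis under Objectives and hypotheses is pooled over patients with rare liver diseases, and the five health systems describe the setting. The low power of a single country is therefore no objection to the plan.

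**Conclusion.** The point holds as a modest matter of efficiency and clarity. The listed primary model omits site or country in a trial whose comparator, counselors and language differ by country, and it leaves the level of its random intercept open.

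The cost depends on an allocation scheme that the article does not describe. If unstratified, power is about 0.81 without a site term and about 0.81 to 0.85 with one, for an assumed site share of 1 to 10% and d = 0.4 on the total SD. If stratified, type I error is about 0.043 to 0.044 at an assumed 5 to 10% share. These figures assume equal sites and a common treatment effect.

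It would be tempting to conclude that the pooled comparison is biased, that the test is anti-conservative or that 240 patients are too few. None of these follows. There is no expected bias, the simulated level without a site term is 0.05 or below, and with the site share unknown the sample size is not shown to be wrong.

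**What to change.** - Add site (country) as a fixed five-level factor to the primary and secondary models. With only five sites, a fixed factor is preferable to a site variance estimated from five units. The cost is 4 degrees of freedom.
- State that the random intercept is for patient.
- State whether the randomisation schedule is stratified by site, and include in the model whatever factors it uses.
- Report group-by-site estimates with confidence intervals descriptively, and keep the confirmatory claim to the pooled effect.

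All of this is a change of text and of one model term. It needs no extra patients or data, and it can still be made after recruitment has started, provided it is fixed before anyone sees outcomes by group.

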#### Peer-counselors

Each partner will recruit approximately seven to ten peer-counselors, i.e. individuals with rare liver diseases (PSC, PBC, AIH), who feel well adjusted to their disease and strive to help others in the adjustment process. Their eligibility will be assessed in structured interviews by social science experts (e.g. psychologists) in each team. Peer-counselors then are invited to a two-day training, which will be held in groups of four to five participants at the national study site. After the training, they receive consultation guidelines and supervision. Over the course of the trial, peer-counselors will complete several counseling cycles. Outcomes will also be assessed in peer-counselors before, once during and after their counseling work and they will be invited to participate in the mixed-method process evaluation.

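### The primary model names no peer-counsellor effect although only the intervention arm is clustered by counsellor, so for any positive counsellor correlation its standard error is slightly too small

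*Protocol article*

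**What the plan says.** All places are in the protocol article.

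- **Who is clustered.** Under The intervention, each intervention patient has a 30-minute telephone session with a peer-counsellor alongside each of the six weekly chapters. Under Peer-counselors: "Each partner will recruit approximately seven to ten peer-counselors", and "Over the course of the trial, peer-counselors will complete several counseling cycles". There are five sites, and Sample size puts the total at about 40 counsellors.
- **Who is not.** Under Effectiveness focus (Procedures), controls receive care as usual alone and are offered the programme only after their last assessment.
- **Sample size.** "we assume a between groups effect size of *d* = 0.4", followed by "Based on two-sided testing with α = 0.05 and 1-β = 0.8, *N* = 100 patients are needed per group", "yielding in *N* = 200 to be analyzed", and an allowance for "approximately 15% loss to follow-up" that leads to 240 randomised. No ICC or design effect is mentioned.
- **Primary model.** Data analysis specifies a hierarchical linear model, fitted by restricted maximum likelihood, with time and group as factors, time as the repeated effect, "the time x group interaction, the baseline outcome score as a covariate, and a random intercept". The level of the intercept is not named. The counsellor is not among the terms.

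**The concern.** This is a partially nested design. Patients in one arm are grouped under the people who deliver the treatment, and patients in the other arm are not grouped at all. Counsellors are lay people with two days of training, so some difference in effect between them is plausible. Patients of the same counsellor would then have correlated outcomes after randomisation.

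A model without that variance component treats every intervention patient as an independent piece of information. Its confidence interval for the primary group difference is then too narrow and its test rejects too often under the null. Adjusting for the baseline score does not cure this, because the counsellor variance arises after baseline.

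The point concerns what the article fixes, not detail left to an analysis plan: the article gives the primary model term by term, and a term that the design calls for is not on the list.

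**Working it through.** **1. Reproduce the stated sample size.** Inputs from Sample size: d = 0.4 (SD 1), two-sided α = 0.05, power 0.80.

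- Normal approximation: n = 2 × (1.96 + 0.842)² / 0.4² = 98.1, so 99 per arm.
- Noncentral t: 100 per arm, power 0.804.
- Loss to follow-up: 200 / 0.85 = 235.3, so 236, against 240 stated.

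The stated 100 per group is therefore the figure for independent observations (design effect 1).

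**2. Patients per counsellor.** Five sites with seven to ten counsellors give 35 to 50.

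- Central case: 100 analysed / 40 = 2.5.
- Low end: 100 / 50 = 2.0.
- High end: 120 randomised / 35 = 3.4.

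**3. Formulas.** Assume equal total variance in the two arms and clustering only in the intervention arm. Let m be the mean number of patients per counsellor and CV the coefficient of variation of caseloads.

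- Intervention-arm design effect: DE = 1 + [(1 + CV²)m − 1] × ICC. For controls, DE = 1.
- True SE / reported SE = √[(1 + DE)/2].
- Type I error = 2 × Φ(−1.96 / SE ratio).
- Power = Φ(0.4 / √[(1 + DE)/n] − 1.96).

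**4. Results for m = 2.5 and even caseloads (CV = 0).** The ICC is an assumption throughout.

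| ICC | DE | SE ratio | Type I error | Power, 100/arm | Power, 102/arm | n/arm for 80% |
|---|---|---|---|---|---|---|
| 0.01 | 1.015 | 1.004 | 5.1% | 80.5% | 81.2% | 99 |
| 0.05 | 1.075 | 1.019 | 5.4% | 79.3% | 80.1% | 102 |
| 0.10 | 1.150 | 1.037 | 5.9% | 77.9% | 78.7% | 106 |

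Example at ICC 0.05: DE = 1 + 1.5 × 0.05 = 1.075; √(2.075/2) = 1.019; 1.96/1.019 = 1.924, which gives 5.4%. The 102 per arm is what the plan expects to analyse: 240 × 0.85 = 204.

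**5. Simulation check.** A t-test that ignores the counsellor, with 100 per arm and 40,000 replicates, rejected a true null in 4.9% of trials at ICC 0, 5.6% at 0.05 and 5.9% at 0.10. This agrees with the formula to within about 0.2 percentage points.

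**6. Uneven caseloads.** The article sets no caseload, so CV = 0.6 is a further assumption.

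- m = 2.5: SE ratio 1.030 and type I error 5.7% at ICC 0.05; 1.058 and 6.4% at ICC 0.10.
- Unfavourable corner, m = 3.4 and ICC 0.10: SE ratio 1.087 and type I error 7.1%.

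These calculations use a single time point without baseline adjustment. The ICC that matters for the planned model is that of the baseline-adjusted outcome.

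**The case against.** **The ICC may be close to zero.** The programme has features that would limit counsellor variance: a self-help manual as one of its two components, training, chapter-by-chapter guidelines, supervision, and an adherence record after each session. At an ICC of 0.01 the effect is negligible (type I error 5.1%). This stands. A reader might infer that the standard error is certainly too small, but the documents support only the conditional statement: too small if the counsellor ICC is positive.

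**The level of the intercept is inferred.** This also stands. The text does not exclude another level, such as site. Only a counsellor intercept, with the repeated effect carrying the within-patient correlation, would cover the problem. Nothing in the section points to that, and half the patients have no counsellor.

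**Part of the remedy is ordinary analysis-plan or database detail.** Agreed. The degrees-of-freedom method and the recording of a counsellor identifier are not faulted as missing. Counsellors already complete a record after each session, so nothing shows that the link between patient and counsellor is lost.

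**The result cannot be carried over to new counsellors.** A reader might infer this, but it goes too far. The implementation questions are answered by the survey and the focus groups, not by the variance structure of the primary model.

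None of this removes the core point. The model is listed term by term, the counsellor is not in it, and the direction of the error for a positive ICC is known.

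**Conclusion.** The point holds as a modest and inexpensive improvement to the primary analysis. For any positive counsellor ICC, the model as written reports too small a standard error and its test exceeds 5%. With even caseloads of 2.5 patients and an ICC of 0.01 to 0.10, the true standard error is 0.4% to 3.7% larger and the type I error is 5.1% to 5.9%. The unfavourable corner examined reaches 8.7% and 7.1%. All of these figures rest on an assumed ICC, and the uneven-caseload figures also rest on an assumed caseload spread.

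A reader might infer that the trial is underpowered or that 240 is the wrong number. The documents do not support that. With 204 analysed, power is about 80% at an ICC of 0.05 and 78.7% at 0.10, before any gain from baseline adjustment, which the calculation does not show. Much larger error rates could be produced by assuming very uneven caseloads, but the article gives no caseload distribution on which to base them.

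**What to change.** - State that the random intercept is the patient's.
- Add to the primary model a counsellor random effect that applies only in the intervention arm, with each control treated as their own cluster.
- Use Satterthwaite or Kenward-Roger degrees of freedom.
- Link a counsellor identifier to each intervention patient in the study database.
- State the counsellor ICC assumed in planning.

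The cost is one model term, one database field and a slightly wider confidence interval for the primary comparison. No additional patients are needed.
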